## Abstract

**Background:**

Early mother–child skin-to-skin contact (SSC) in the first 2 h postpartum is highly beneficial for both mother and child. However, cases have been reported of newborns who have experienced apparently life-threatening events (ALTEs) or sudden death during this procedure. The causes of these events are unknown. Newborn’s prone position could influence the onset of these events but there is very little evidence to support any recommendation. We hypothesize that newborns’ breathing obstruction episodes increase as mothers lie more horizontally.

The main objective of this study is to compare the occurrence of desaturation and bradycardia episodes as a function of mother’s bed incline.

The study is designed as a randomized, controlled, assessor blind, multicenter, superiority trial with two parallel groups and 1:1 allocation ratio.

**Methods:**

The study participants will be full-term healthy mother–newborn dyads from ten hospitals in Spain. Participants will be randomly assigned to one of two study arms defined by mother’s bed inclination (45° or 15°). The planned sample size is 5866. Centralized permuted blocks randomization and assessor blinding will be implemented.

The newborns will be monitored remotely with pulse oximetry, from 10 min to 2 h after delivery. We established SO_2_ and heart rate (HR) limit alarms, as well as an action protocol in the event of alarm activation.

The primary outcome is the number of healthy newborns who undergo episodes of SO_2_ ≤ 90%. Secondary outcomes are the mean SO_2_ level, the number of newborns who experience episodes of SO_2_ ≤ 85%, the time to SSC discontinuation due to abnormal SO_2_ or HR, and episodes of HR < 111 beats per minute (bpm) or > 180 bpm. Subgroups and pooled analysis will be performed to identify if breast-feeding and mother and child positions favor the occurrence of desaturation or bradycardia episodes.

**Discussion:**

A simple intervention such as modifying mother’s bed angle of inclination while in SSC with her child during the first 2 h postpartum could favor newborn’s hemodynamic and respiratory stabilization and thus contribute to reducing the onset of ALTEs.

**Trial registration:**

ClinicalTrials.gov, NCT02585492. Registered on 22nd October 2015.

**Protocol version:**

2 (30th June 2015).

**Electronic supplementary material:**

The online version of this article (10.1186/s13063-019-3256-0) contains supplementary material, which is available to authorized users.

## Introduction

### Background and rationale

Placing newborns in skin-to-skin contact (SSC) with their mother’s abdomen immediately after birth is currently recommended. This intervention has been recommended by the Baby Friendly Hospital Initiative [1] and the American Academy of Pediatrics [2] and is listed in Australian [3], Canadian [4], and British [5] guidelines. In Spain, this intervention is recommended by, among others, the Spanish Ministry of Health [6].

SSC promotes the establishment of an affective link between parents and child, a crucial part of the child’s survival and emotional development [7, 8]. SSC also improves the mother’s perceptions of her child, her maternal skills, and the newborn’s physiological stability [9–11]. The practice promotes the start and duration of maternal lactation, prolonging it by a mean of 43 days.

Coinciding with the widespread use of this intervention, however, cases have been reported of newborns who have experienced apparent life-threatening events (ALTEs) or sudden death in the first 2 h postpartum. These newborns had a gestational age ≥ 37 weeks, were born vaginally, and were apparently healthy [12–16]. These events have been reported in various countries [16–27]. Although there are still no appropriate registries, the global incidence rate appears to vary between 2.5 and 3.2/100,000 births, and the mortality rate varies between 0.8 and 1.8/100,000 births [16, 20]. The children who survive these events frequently experience severe neurological sequela [14, 15, 18, 19, 24–26].

The cause of these episodes is unknown [12, 13, 16, 17, 21, 22, 24], although the first 2 h after delivery are a critical period for newborns. A number of authors consider that newborns are more vulnerable to stressful hypoxic factors during this period due to airway obstructions (a condition that could arise when lying in decubitus prone on the mother’s body or breastfeeding) [12, 14, 16, 17, 19, 21, 25–27]. For other authors, these are newborns with prenatal impairment not initially manifested [20]. A number of authors have suggested that these events could be explained by a predominance of vagal tone during breastfeeding [13, 26]. These events have been observed more frequently in primiparous women, those who are tired or sleepy after delivery and those who were not monitored properly during SSC or while breastfeeding [12–17, 19–22, 24, 26, 27].

Due to the low incidence of ALTEs or sudden deaths in the first 2 h of life in SSC, it is very difficult to conduct prospective studies that enable the assessment of the efficacy of an intervention to prevent the ALTEs and sudden deaths. However, the fact that these events occur during the 2 h after delivery, a period in which most newborns are in a healthcare center, makes it feasible to design studies that evaluate the effect of various interventions on certain biological parameters that can be continuously monitored, such as SO_2_ and HR. Instability in either of these two parameters could precede these devastating events.

We found no information in the reviewed literature on the influence of the angle at which the mother’s bed is inclined while in SSC on SO_2_ and HR outcomes. Only a case study by Rodríguez-Alarcón et al. [27] recommends that the mother sit at 30° to 45° above the horizontal with a pillow behind the head but provides no information from any study to justify this recommendation. Given that the newborn’s prone position and the presence of circumstances that favor asphyxial episodes could influence the onset of these events, we could postulate that the more the mother is inclined, the more chances there are that the newborn will be in a situation that obstructs breathing during this critical period of life.

We therefore decided to conduct a randomized, multicenter clinical trial to compare the number of healthy newborns who experience episodes of SO_2_ ≤ 90% during the first 2 h after birth while in SSC with their mother while she is sitting up at a 45° or 15° angle above the horizontal plane of the bed.

### Objectives

The main objective is to compare the proportion of healthy newborns who undergo at least one episode of SO_2_ ≤ 90% between the two groups.

As secondary objectives, we will compare.the mean SO_2_ levelthe proportion of newborns who experience at least one episode of SO_2_ ≤ 85%the rate at which SSC is interrupted due to abnormal SO_2_ or HRepisodes of HR < 111 beats per minute (bpm) or > 180 bpm

An additional secondary objective will be to identify positions for the mother and newborn that favor desaturation or bradycardia episodes.

### Trial design

The study is designed as a randomized, controlled, assessor blind, multicenter, superiority trial with two parallel groups and 1:1 allocation ratio.

The study has been approved by the Clinical Research Ethics Committee of the coordinating center (Hospital 12 de Octubre) and of each participating center. Additional file 1 contains the list of SPIRIT confirmation for the study.

## Methods

### Study setting

This study emerged from the research group setting of the Spanish Collaborative Research Network for Maternal and Child Health (SAMID Network; reference RD12/0026/0007) and is financed by the Carlos III Health Institute of Spain. Ten Spanish hospitals from various regions and healthcare levels are participating in the study, which together cover approximately 27,000 births a year. The coordinating center is Hospital 12 de Octubre of Madrid. The research groups involved in the study have experience in participating and coordinating relevant European and international projects.

These hospitals have beds with adjustable tilt for the women. Each of the centers is equipped with a remote SO_2_ and HR monitoring system (Masimo Patient SafetyNet®) for the newborns and have computer systems that provide 24-h access to the study’s computer platform to conduct the randomization and data entry into the electronic notebook. The mean number of researchers per center is 10, with a range of 2–20.

### Eligibility criteria for participants

All women who, at the start of labor, meet the inclusion criteria and none of the exclusion criteria (prerandomization criteria) and who have signed the consent form (see Additional file 2) will be included in the study and randomized using an ad hoc computer platform. In addition to the prerandomization exclusion criteria, we have established postrandomization criteria that will require withdrawal from the study, given that some events that occur during delivery may affect the newborn well-being. Table 1 lists the prerandomization inclusion and exclusion criteria, and Table 2 lists the postrandomization withdrawal criteria. Once 10 min have passed, and it is confirmed that none of the delivery- or neonate-related postrandomization withdrawal criteria have been met, all participating dyads will be included in the primary analysis.

**Table 1 Tab1:** Prerandomization inclusion and exclusion criteria

*Prerandomization inclusion criteria*	
Women who meet the following criteria at the start of labor are considered candidates:	
(a) pregnant with a single fetus	
(b) monitored or partially monitored pregnancy (women who underwent ultrasonography at week 20 of their pregnancy but not during the first or third trimester or who did not undergo all trimester laboratory tests)	
(c) pregnancy proceeding normally or with mild disease (gestational diabetes treated exclusively with diet or arterial hypertension [with no diagnosis of preeclampsia] controlled with a single drug)	
(d) end of pregnancy at full term (37^+ 0^–41^+ 6^ gestational age)	
(e) temperature at start of labor ≤ 38 °C	
(f) presence of companion during the 2 h after delivery	
(g) mother’s wish for SSC	
*Prerandomization exclusion criteria*	
We excluded pregnant women before the randomization who met one or more of the following criteria:	
(a) consumption during pregnancy of tobacco, alcohol, drugs, or medication with sedative effects (opioids, antiepileptic drugs, antipsychotics, anxiolytics, hypnotics, antidepressants, and plants with sedative effects)	
(b) non-mild disease during pregnancy	
(c) prenatal diagnosis of chromosomal disorders or major malformation	
(d) prenatal diagnosis of intrauterine growth retardation with any degree of flow impairment, as well as an “abnormal” fetal size for gestational age (due to malformation, intrauterine infection, etc.)	
(e) lack of companion during the first 2 h postpartum

**Table 2 Tab2:** Postrandomization criteria for withdrawal from the study

*Delivery related*	
(a) caesarean section or instrumental delivery (forceps, vacuum)	
(b) maternal fever > 38 °C	
(c) maternal hemodynamic instability (hypotension, tachycardia, impaired consciousness, poor perfusion, notable pallor) or any other type of ailment	
(d) umbilical cord prolapsed	
(e) signs of fetal “distress”, with fetal scalp pH < 7.25 or umbilical artery pH < 7.20	
(f) any other obstetric complication	
(g) use of sedatives or relaxants during or after delivery	
*Neonate related*	
(a) need for resuscitation measures	
(b) intrapartum-diagnosed major malformation	
(c) Apgar score ≤ 7 at 1, 5, or 10 min	
(d) presence of symptoms before 10 min of life	
(e) birth weight < 2300 g or > 4500 g	

### Interventions

Before starting patient enrollment, all participating centers have agreed upon the SSC procedure and the study intervention. Additionally, the coordinating center has conducted face-to-face training sessions in each of the hospitals.

When a possible case is identified, consent from the pregnant woman will be requested. Once the woman has agreed to participate, she is shown a number of photographs of how to perform SSC (Fig. 1; “Models for mother’s and newborn’s positions for 15° and 45° inclination”). The woman is told to record the moment(s) when the newborn latches on to the breast. The woman’s data are subsequently entered into the computer platform to proceed with the randomization. After the delivery, the researcher attending the birth will verify that the case does not meet any of the postrandomization withdrawal criteria. The pulse oximetry apparatus (noninvasive Radical-7 Signal Extraction PulseCO-Oximeter® monitor equipped with Masimo Rainbow SET® technology) is then plugged into the power outlet and to the data collection and is subsequently turned on. The pulse oximeter alarms have been established at 91% as the lower limit for SO_2_; the upper limit has not been set. For the HR, the lower limit alarm has been set to 111 bpm and the upper limit to 180 bpm.

**Fig. 1 Fig1:**
[figure not shown]
Models for mother’s and newborn’s positions for 15° and 45° inclination

During the first 10 min after delivery, with the newborn in SSC, the pulse oximeter sensor is attached (Masimo, LNCS® Series Neo-L adhesive sensor) on the right hand or wrist (preductal SO_2_). Considering the LNCS® sensor directions for use, the precision of the sensors is ± 3% for SO_2_ with or without movement and for the HR ± 3 bpm without movement and ± 5 bpm with movement. The saturation accuracy of the neonate was validated on adult volunteers and 1% was added to account for the properties of fetal hemoglobin. During these first 10 min after birth, the mother’s bed position is changed according to the corresponding randomization group (45° or 15° above the horizontal). To standardize the intervention, two cardboard models (15° and 45°) have been manufactured that exactly reproduce the angle (Additional file 1). During this period, diaper placement is the only intervention allowed.

At 10 min after birth, the sensor cable is attached to the pulse oximeter. After the connection, the pulse oximeter begins continuously recording the HR and SO_2_, storing the data and signal quality every 2 s. The pulse oximeter remains connected to a central station (Patient SafetyNet System, version V.4610, Masimo®) next to the newborn and mother for the 2 h of the study. The system transmits the data to the central station in real-time every second, displaying them on a monitor. The pulse oximeter’s alarms can be silenced and the screen light turned off so as to disturb the mother and newborn as little as possible. The alarms can be silenced in both the monitor and pulse oximeter. The pulse oximeter’s lighting can be reduced to a minimum to disturb the mother and newborn as little as possible. A practitioner is continuously monitoring the display and can respond to an alarm. As a safety mechanism, four locator-searchers (nurse, resident physician, staff physician, and supervising staff physician) provide alerts on the various alarms generated during the recording.

During the intervention period, the newborns remain at all times in SSC with their mother and will not undergo any procedure. If the newborn is separated from their mother for a reason other than those contemplated in the study (see alarm management protocol below), the recording will be stopped and the newborn will be removed from the study.

The mother may place a pillow behind her head but not behind her back and may choose her position in the bed, provided the assigned inclination angle is not changed (Fig. 1).

In those hospital centers in which the delivery and immediate postpartum do not take place in the same room, the transfer will be performed with the newborn in skin-to-skin contact, and the time of the transfer will be recorded. The monitor alarm, which will occur when disconnecting the pulse oximeter, will thereby be accounted for.

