**Fig. 2 Fig2:**
[figure not shown]
Action protocol when an alarm sounds or a professional assessment is requested

Table 3 shows the data that will be collected when visiting the newborn for an assessment. The mother’s and newborn’s positions will be documented according to a series of model images created for each degree of inclination (Fig. 1; “Models for mother’s and newborn’s positions for 15° and 45° inclination”).

**Table 3 Tab3:** Data recorded in case of alarm or if a professional assessment is requested

a. Number of alarms for this patient	
b. SO_2_, HR, and time	
c. Minimum SO_2_ during the episode and corresponding HR	
d. Minimum or maximum HR as appropriate and corresponding SO_2_	
e. Time to once again reach an SO_2_ > 90%	
f. Position of the mother and child	
g. Probable corresponding factor	
h. Child’s clinical situation	
i. If it entails terminating the procedure	
j. Possibility of airway obstruction in the child	

The practitioner will classify the alarm as clinical or nonclinical depending on whether the events that justify these alarms are clinical (CEs) or nonclinical events (NCEs), respectively. The CEs can, in turn, be clinically relevant (CREs) or nonclinically relevant events (NCREs).

NCEs do not entail that the intervention is terminated and can occur due to excessive ambient light, problems with the pulse oximeter’s connection cable or sensor, low battery levels, interference, and lack of system connectivity or availability.

The CEs include an SO_2_ < 91%, a HR > 180 bpm or < 111 bpm, and a newborn with symptoms. The protocol to be followed when clinical alarm sounds is shown in Figs. 3 and 4 (Fig. 3, action protocol when a SO_2_ < 91% clinical alarm goes off; Fig. 4, action protocol when a HR > 180 or < 111 bpm clinical alarm sounds). A CE is considered nonclinically relevant (NCRE) if the newborn is asymptomatic and the event can be explained by a technical problem (insufficient signal capture) or by the newborn’s condition at that moment (crying, newborn handling by the mother, movement, etc.). NCREs do not entail the termination of the intervention.

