### Outcomes

The main outcome collected in both intervention groups will be the proportion of healthy newborns who undergo at least 1 episode of SO_2_ ≤ 90%.

The following secondary outcomes will also be recorded:The mean SO_2_ level and HR in the first hour, in the second hour, and for both hours combined.The proportion of newborns who undergo at least one episode of SO_2_ ≤ 85%.The proportion of SSC interruption due to a medical indication.The number of HR episodes < 111 bpm and > 180 bpm.The mother’s posture (right lateral decubitus, left lateral decubitus, or supine) and that of her child (right lateral decubitus, left lateral decubitus, supine, or prone) at the time of the episode of SO_2_ ≤ 90% or HR < 111 bpm.

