### Statistical methods

As we estimate a relevant proportion of estimated postrandomization exclusions, we will perform a modified intention to treat analysis.

The study will employ a two-tailed significance level of 5%. The confidence intervals will be 95%. The main assessment criterion is the presence of an episode of SO_2_ ≤ 90%. We will perform an unadjusted analysis of the intervention’s effect with chi-squared test.

The distribution of the baseline prognostic variables will be analyzed with the mean and standard deviation for the continuous variables (we expect a normal distribution) and with numerators/denominators and percentages for the categorical variables. *P* values will not be included, but we will indicate the variables that have a strong association that could have a confounding effect—even if the distributions in the two study groups are not very different—and the variables with large differences between the groups that could have a confounding effect, even those with a poor association. Stratified analysis and logistic regression modeling will be performed on the primary outcome to take into account covariates (i.e., exploring the possible effect of modification of breast feeding, adjusting for relevant covariates, etc.). The strategies for missing-data imputation and the subgroup analysis will be documented a priori.

The statistical analysis will be conducted using the software environment R [28].

An independent committee, which will include an independent biostatistician, will review the results of the interim analysis.

The study will be halted if differences in the main outcome show a *p* value below 0.001 to protect the overall type I error of the trial. The study will also be interrupted on safety grounds due to any other results that show a negative effect on the child or mother considered relevant by the committee.

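### Newborns separated from the mother after the 10-minute check are both kept in the primary analysis and removed from the study, and SSC interruption is defined three ways

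*Protocol article*

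**What the plan says.** **Primary analysis set.** Under Eligibility criteria for participants, Table 2 is introduced as "postrandomization criteria that will require withdrawal from the study". Once 10 minutes have passed and no Table 2 criterion is met, "all participating dyads will be included in the primary analysis".

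**Later separation.** The Interventions section, describing the 2-hour monitoring period, adds a further rule: "If the newborn is separated from their mother for a reason other than those contemplated in the study", with a pointer to the alarm management protocol, "the recording will be stopped and the newborn will be removed from the study".

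**What the alarm protocol covers.** The text on alarms deals with newborn events and technical faults: "The CEs include an SO_2_ < 91%, a HR > 180 bpm or < 111 bpm, and a newborn with symptoms". A clinically relevant event ends the intervention, and a symptomatic newborn is one of the grounds for calling an event clinically relevant.

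**Analysis label.** Statistical methods announces a modified intention-to-treat analysis because of the expected postrandomization exclusions. It does not say whether separations after 10 minutes are among them. It promises that missing-data strategies will be documented in advance.

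**SSC interruption.** The Abstract gives "the time to SSC discontinuation due to abnormal SO_2_ or HR". The Objectives give a rate, with the same two causes. The Outcomes section gives "The proportion of SSC interruption due to a medical indication".

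**The concern.** A newborn who passes the 10-minute check and is separated at, say, 50 minutes for a reason outside the alarm protocol is in the primary analysis under one section and out of the study under another. The removal rule acts after the bed has been set to 15° or 45°, so separation could depend on the assigned angle. If the rule is followed, desaturation episodes already on the recording drop out of the comparison. If the Eligibility rule is followed with nothing more said, a truncated recording can pass as one with no episode.

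Table 2 adds to the doubt. Items (c) maternal instability or other ailment, (f) other obstetric complication and (g) sedatives during or after delivery have no time limit, whereas the neonatal symptoms item has an explicit 10-minute limit. A late maternal event could therefore be treated as a Table 2 withdrawal at one centre and not at another.

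The interruption outcome has its own problem. A time, a rate and a proportion are different quantities, and abnormal SO2 or HR is a narrower cause than a medical indication.

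**Working it through.** **1. The rules side by side**

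| Event after 10 min | Eligibility | Interventions | Table 2 |
|---|---|---|---|
| Separation under the alarm protocol | kept | not removed | not listed |
| Non-medical separation | kept | removed | not listed |
| Maternal medical separation | kept | removed, if outside the alarm protocol | unclear: (c), (f), (g) untimed |

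The second row is a direct conflict. The third is a conflict or an ordinary withdrawal, depending on how Table 2 is timed.

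**2. The plan's own figures**

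- For 9% v 6%, two-sided 5%, 80% power, pooled variance with continuity correction: 1275 per group, as stated (1209 without the correction).
- 2550/0.5 = 5100, and 5100 × 1.15 = 5865, against 5866 stated.
- Expected to pass the 10-minute check: 5866 × 0.5/2 = 1466.5, about 1467 per arm. Uncorrected power for 9% v 6% is 87% at that size (82% at 1275).

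**3. Size of the effect on the primary comparison**

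The documents give no separation rate. I assume 2% (29 per arm), with a range of 1% (15) to 5% (73).

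*Separation unrelated to episodes, on average halfway through the recording.* The chance of an episode in half the window, at constant hazard, is 1 − (1 − 0.09)^0.5 = 4.61% and 1 − (1 − 0.06)^0.5 = 3.05%. Kept, with unseen time counted as no episode, the arm rate is (1 − f) × p + f × half-window rate. Removed, the arm rates stay at 9% and 6%.

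| Separated, 15° v 45° | Kept | Removed |
|---|---|---|
| 2% v 2% | 8.91 v 5.94, difference 2.97 | 3.00 |
| 5% v 5% | 8.78 v 5.85, difference 2.93 | 3.00 |
| 5% v 2% | 8.78 v 5.94, difference 2.84, power 84% | 3.00, power 86% |

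*Separation related to episodes.* Let 9% and 6% be the proportions with a recorded episode when everyone is kept, and let a share q of separated newborns already have one. Kept gives 3.00 points by construction. Removed gives (p − q × f)/(1 − f) in each arm.

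| Separated, 15° v 45° | q | Removed | Difference |
|---|---|---|---|
| 5% v 2% | 20% | 8.42 v 5.71 | 2.71, power 80% |
| 5% v 2% | 30% | 7.89 v 5.51 | 2.38, power 72% |
| 2% v 5% | 30% | 8.57 v 4.74 | 3.83 |
| 5% v 5% | 30% | 7.89 v 4.74 | 3.16 |

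The first two rows understate the difference and the third overstates it. With equal separation the shift is small even when episodes are related to it.

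**4. The interruption outcome**

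| Section | Metric | Cause |
|---|---|---|
| Abstract | time to event | abnormal SO2 or HR |
| Objectives | rate | abnormal SO2 or HR |
| Outcomes | proportion | medical indication |

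The clearest difference lies within the newborns. One with symptoms but normal SO2 and HR can have SSC ended as a clinically relevant event. That newborn counts under Outcomes but not under the Abstract or Objectives.

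**The case against.** **The removal may mean only that recording stops.** The sentence states both stopping the recording and removing the newborn, and it does not say that data collected up to then are kept. Elsewhere the article uses withdrawal from the study for dyads that leave the primary analysis. The charitable reading is possible but has to be supplied by the reader.

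**Table 2 may already cover late maternal events.** This stands in part. Items (c), (f) and (g) can be read that way, and removal would then agree with the modified intention-to-treat label. A reader might infer that every late maternal separation is a proven contradiction; the text does not support that. What it does support is a conflict for reasons outside Table 2, and an unclear time limit for the rest.

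**The numbers are assumed.** This also stands. A reader might infer that power falls to 72%. That needs unequal separation together with episode rates of 20% to 30% among separated newborns, well above the planned 9% and 6%, and the documents give no reason to expect this. When separation is unrelated to episodes, keeping and removing give nearly the same answer.

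**The interruption conflict over maternal causes needs two readings at once.** A dyad removed under Interventions cannot count under Outcomes, and the only medically indicated termination described is the clinically relevant event. A reader might infer that the result could swing from a clear benefit to none according to how maternal causes are counted. That would need maternal and newborn causes to offset each other by arm, which nothing in the documents suggests. The difference in metric and the symptomatic newborn do not depend on that reading.

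**Maternal harm.** A reader might infer that the interruption outcome is the only route by which maternal harm reaches the committee. It is not: the stopping ground is "any other results that show a negative effect on the child or mother considered relevant by the committee", which is not confined to listed outcomes.

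**The SAP will settle truncated recordings.** It may well do so, and their detailed handling is no finding here. Which dyads are in the primary set is stated in this article, in two incompatible ways. Figs. 2 to 4 are not shown, but their captions and the text concern newborn alarms and assessment.

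**Conclusion.** The point holds as a conflict between two stated rules and as an avoidable exclusion after the intervention has begun. Its size cannot be determined from the documents. With equal separation of 2% to 5% unrelated to episodes, the planned 3.0-point difference moves by less than 0.1 point. With 5% v 2% and no relation to episodes, the two rules give 2.84 and 3.00 points. A material shift, to between 2.38 and 3.83 points on the assumptions shown, needs separation that both differs by arm and is related to desaturation. The case for acting rests on cheap protection against bias, not on a demonstrated loss of power. The planned sample size is unaffected.

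The inconsistent definition of SSC interruption is a separate and plain fault. It holds whatever removal is taken to mean.

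**What to change.** **Interventions.** State that the recording stops but the dyad stays in the primary set fixed at 10 minutes. Episodes recorded before separation count. Dyads separated without an episode are handled by the missing-data strategy already promised under Statistical methods. Add one sensitivity analysis that excludes separated dyads.

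**Table 2.** State that its criteria apply only up to 10 minutes after birth.

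**Abstract, Objectives, Outcomes.** Use one metric and one definition of SSC interruption: termination under the alarm protocol for a clinically relevant event, meaning abnormal SO2, abnormal HR or a symptomatic newborn. Limiting it to abnormal SO2 or HR would drop symptomatic newborns. Report all other separations, maternal included, as a separate count by arm.

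**Cost.** Wording changes and one sensitivity analysis. The downside is that partly recorded dyads enter the primary set and depend on the missing-data rule. The time and reason of separation must also be available. Table 3 records termination only for alarms and requested assessments, and Table 4 lists neither item, so their availability should be checked for dyads already enrolled and the two fields added to the case report form if absent.
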